**Figure 2 F2:**
[figure not shown]
Lower confidence limit plot for inoculation-induced *Neisseria lactamica* (Nlac) colonisation.

We expect to screen at least 24 volunteers to reach our target of 20 inoculations, allowing for 10% dropout and 10% baseline natural *N. lactamica* carriage.^18^ It is not clear how maternal or neonatal antibiotics may influence *N. lactamica* carriage and microbiota. At the Principal Investigator’s discretion, an additional volunteer may be enrolled and inoculated for every volunteer (or neonate) who receives antibiotics after inoculation, up to a maximum of 10 additional volunteers.

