### Sample processing

#### *N. lactamica* identification

Working in a class 2 microbiological safety cabinet in a Containment Level 2 laboratory, all respiratory samples will be suspended in 1 mL storage medium (10% glycerol in 0.1% diethylpyrocarbonate (DEPC)-treated water). Agar selective for *N. lactamica* (GC agar supplemented with 5-bromo-4-chloro-3-indolyl-β-galactopyranoside (X-gal); Thermo Fisher Scientific, Basingstoke, UK) will be inoculated with sample solution, and all remaining sample solution will be split into 200 µL aliquots for storage in a secure, temperature-monitored −80°C freezer. Following 24–48 hours incubation, colonies with typical *N. lactamica* morphology (blue on GC X-gal agar) will undergo identification by oxidase reaction, Gram stain, microscopy and analytical profile index (API-NH, bioMérieux, Lyon, France) or matrix-assisted laser desorption/ionisation time-of-flight (MALDI-TOF; Bruker, Coventry, UK). *N. lactamica* density will be quantified and isolates will be stored at −80°C. Breastmilk will also be plated onto selective agar to examine for evidence of *N. lactamica*, and residual samples will be stored at −80°C for microbiome analysis.

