### Sample size

To our knowledge, this proof-of-concept represents the first respiratory controlled human infection study in pregnancy. As such, it is not possible to accurately define the sample size needed to conclusively rule out induced horizontal transfer of *N. lactamica*. A pragmatic sample size of 20 inoculated volunteers has been selected: based on our earlier work, *N. lactamica* colonisation is expected in 18 (90%) of volunteers inoculated with 10^5^ CFU *N*. *lactamica*. This sample would therefore fail to detect horizontal transfer only if it occurs in less than 1 in 18 infants (<6%), in which case it would be impractical and even unethical to pursue horizontal *N. lactamica* controlled human infection as a method of studying and manipulating infant commensalisation. By 1 month of age, 2.3% of infants naturally carry *N. lactamica*.^17^ Based on a plot of lower confidence limits against observed infant *N. lactamica* colonisation for a sample of 18 experimentally-colonised volunteers, infant *N. lactamica* colonisation greater than 22% (95% CI (2.3% to 41.7%)) would demonstrate that inoculation-induced carriage exceeds natural *N. lactamica* carriage (figure 2).

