### Statistical analysis

The primary endpoint will be expressed as a proportion N/M, where:

M=Number of mothers colonised with *N. lactamica*.N=Number of neonates (aged 0–31 days) colonised with the same strain of *N. lactamica* as their own mother.‘Colonised’=evidence of *N. lactamica* by culture of upper respiratory swabs (using selective media and confirmation by API or MALDI-TOF) on at least one visit.‘Same strain’=confirmed using Y92-specific *N. lactamica* PCR for inoculated volunteers, or whole genome sequencing for volunteers already naturally carrying *N. lactamica* at screening.

Subgroup analysis will be performed, to compare inoculated mother–infant pairs with naturally colonised mother–infant pairs, and to compare pairs where the mother or infant received antibiotics with pairs not receiving antibiotics.

Specific bioinformatic analysis strategies will depend on the quantity and quality of genomic data produced during the study, and on the rates of *N. lactamica* colonisation observed. Broadly speaking, microbiome bioinformatic pipelines (eg, QIIME2 and R packages) will be used to perform taxonomic classification, calculation of alpha and beta diversity and data visualisation.

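### Extra volunteers after antibiotic use are optional at the investigator's discretion, with infant cultures not stated to be withheld, and the 22% success bar fits only 18 colonised mothers

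*Protocol article*

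**What the plan says.** All references are to the protocol article.

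- **Sample size, target.** "A pragmatic sample size of 20 inoculated volunteers has been selected", and "colonisation is expected in 18 (90%) of volunteers inoculated with" the stated dose.
- **Sample size, success bar.** Natural infant carriage at 1 month is put at 2.3%. The bar is worked out "for a sample of 18 experimentally-colonised volunteers": infant "colonisation greater than 22% (95% CI (2.3% to 41.7%)) would demonstrate that inoculation-induced carriage exceeds natural" carriage. No bar is given for any other number.
- **Sample size, paragraph after Figure 2.** Because the effect of antibiotics on carriage is unknown, at the Principal Investigator's "discretion, an additional volunteer may be enrolled and inoculated for every volunteer (or neonate) who receives antibiotics after inoculation". The cap is 10.
- **N. lactamica identification.** Cultures are read quickly: "Following 24–48 hours incubation, colonies with typical" appearance go on to identification.
- **Statistical analysis.** The primary endpoint is N/M, where M counts colonised mothers and N counts neonates aged 0–31 days who carry their own mother's strain. Antibiotic exposure does not remove a pair from either count. It enters only through a subgroup analysis, "to compare pairs where the mother or infant received antibiotics with pairs not receiving antibiotics".
- **Strengths and limitations.** There is no control group.

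**The concern.** Three provisions, each reasonable alone, combine badly.

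First, antibiotic receipt opens a slot but does not fill it; whether to use the slot is left open. The article does not say that the person deciding must be unaware of infant cultures. The choice to enlarge the sample could therefore depend on how many infants are already positive. If slots tend to be used while the running rate is low and left unused once it is high, N/M is biased upward. That proportion is the main product of a proof-of-concept study.

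Second, exposed pairs stay in N/M, so the extra women enlarge M and do not replace anyone.

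Third, the bar was derived for one value of M. Once M grows, the 22% figure and the confidence-limit reasoning behind it can give opposite answers on the same data, whatever the investigator's motives.

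**Working it through.** **Inputs.** From Sample size: 20 inoculated, 90% colonised, natural carriage 2.3%, bar 22% with 95% CI 2.3% to 41.7% for 18, and at most 10 extra. Assumption: the 90% rate also holds among extra volunteers.

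**1. Size of the extension.** 10/20 = +50%, so up to 30 inoculated. Expected M goes from 0.9 × 20 = 18 to 0.9 × 30 = 27.

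**2. Reproducing the article's bar.** Use the normal-approximation interval p ± 1.96 × √(p(1 − p)/k), with p = 0.22.
- k = 18 − 1 = 17: √(0.1716/17) = 0.1005; 0.22 ± 0.1969 = 2.31% to 41.69%. This matches the stated interval.
- k = 18: 2.86% to 41.14%, which does not match.

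The article's method is therefore this interval with k = M − 1.

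**3. The same method at larger M.** Solve p − 1.96 × √(p(1 − p)/(M − 1)) = 0.023.

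| M | Bar by the article's method | Infants needed to exceed 22% |
|---|---|---|
| 18 | 22.0% | 4 |
| 20 | 20.4% | 5 |
| 24 | 18.0% | 6 |
| 27 | 16.6% | 6 |

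A direct conflict: 5/27 = 18.5%. With k = 26 the lower limit is 0.1852 − 1.96 × √(0.1852 × 0.8148/26) = 3.6%. That lies above 2.3%, yet 18.5% fails a 22% bar.

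**4. Worst-case result-driven extension.** Start at M = 18. Add one colonised pair at a time up to M = 27, and stop as soon as the observed rate exceeds 22%. Probabilities come from exact binomial recursion.

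| True rate | P(>22%), M fixed at 18 | P(>22%), M fixed at 27 | P(>22%), extended on results | Mean reported rate when extended |
|---|---|---|---|---|
| 2.3% | 0.00066 | 0.00003 | 0.00069 | about 2.3% |
| 10% | 0.098 | 0.047 | 0.115 | 10.5% |
| 15% | 0.280 | 0.210 | 0.335 | 16.1% |
| 20% | 0.499 | 0.461 | 0.589 | 21.3% |

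Upward bias is 16.1 − 15 = 1.1 points at a true 15%, and 21.3 − 20 = 1.3 points at a true 20%. False success at 2.3% is essentially unchanged.

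**5. An exact limit at the observed M.** The two-sided 95% Clopper-Pearson lower limit exceeds 2.3% from 3 infants upward at every M from 18 to 27 (3/18: 3.58%; 3/27: 2.35%). False success at 2.3% is P(X ≥ 3) = 0.0077 at M = 18 and 0.0236 at M = 27. Since the count needed stays at 3, worst-case extension from 18 to 27 also gives 0.0236, below the nominal 0.025.

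**The case against.** **This is error inflation.** A reader might infer that the discretion seriously raises the false-positive rate. The figures do not support that. At the comparison rate of 2.3%, the worst case under the 22% bar moves only from 0.00066 to 0.00069. The 33.5% at a true 15% is not a false-positive rate, because 15% does exceed natural carriage. The difference between 0.0077 and 0.0236 under an exact limit comes from the larger M and stays within the nominal level.

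**The sample cannot grow on results alone.** This stands. Each extra needs an antibiotic event after inoculation, the cap is 10, a reason is given, and planned antibiotic use is an exclusion. An infant's negative status is also final only after the visit at 28 ± 3 days, and counting toward N needs strain confirmation. A completed look after every added pair is therefore unrealistic. Early positives could still be known when a slot is decided.

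**22% is only a planning figure.** This stands in part. The Statistical analysis section states no decision rule and never applies 22% to a larger M. If it were applied, it would be stricter than the article's own method requires. It remains the only criterion given for exceeding natural carriage, and it is tied to 18.

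**Silence is not a statement.** This is also fair. An article may leave access to results to the full protocol, and it does not call the study open-label. The discretion itself, the cap, the single bar and the N/M definition are stated, however, and the point rests on how they combine.

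**Conclusion.** The concern holds as a weakness of moderate size. Optional additions with no stated separation from infant cultures allow a small upward bias in N/M, about 1 percentage point in the worst case examined (16.1% for a true 15%). This is an upper bound: it needs enough antibiotic events to add nine colonised pairs, each infant's result known before the next decision, and 90% colonisation among the extra women. For scale, the article's own interval runs from 2.3% to 41.7%.

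The firmer part does not depend on anyone looking at results. If the extension is used, the 22% bar no longer corresponds to a lower limit of 2.3%; by the article's method the matching bar falls to 16.6% at M = 27. Neither part shows a meaningful rise in false success against natural carriage, nor that additions have been or would be steered by results.

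**What to change.** 1. Remove the case-by-case choice. Either make each addition automatic on recorded antibiotic receipt after inoculation, up to the existing cap of 10, or have it decided by someone without access to infant culture results. Settle which before the first infant culture is read.
2. Leave the denominator as colonised mothers, and state that antibiotic-exposed and added inoculated pairs count in it. Changing to all inoculated pairs would be a different endpoint and is not needed here.
3. Judge whether carriage exceeds 2.3% by an exact lower confidence limit at the observed M, in place of a fixed 22%.
4. Report antibiotic-free pairs as a named supportive analysis.

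The cost is a change of protocol wording and the loss of flexibility over added enrolment. The cap and the reason for adding volunteers are unaffected.

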### Statistical analysis

The primary endpoint will be expressed as a proportion N/M, where:

M=Number of mothers colonised with *N. lactamica*.N=Number of neonates (aged 0–31 days) colonised with the same strain of *N. lactamica* as their own mother.‘Colonised’=evidence of *N. lactamica* by culture of upper respiratory swabs (using selective media and confirmation by API or MALDI-TOF) on at least one visit.‘Same strain’=confirmed using Y92-specific *N. lactamica* PCR for inoculated volunteers, or whole genome sequencing for volunteers already naturally carrying *N. lactamica* at screening.

Subgroup analysis will be performed, to compare inoculated mother–infant pairs with naturally colonised mother–infant pairs, and to compare pairs where the mother or infant received antibiotics with pairs not receiving antibiotics.

Specific bioinformatic analysis strategies will depend on the quantity and quality of genomic data produced during the study, and on the rates of *N. lactamica* colonisation observed. Broadly speaking, microbiome bioinformatic pipelines (eg, QIIME2 and R packages) will be used to perform taxonomic classification, calculation of alpha and beta diversity and data visualisation.

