## Methods and analysis

### Study overview

In this prospective controlled human infection study, 20 healthy pregnant women will receive nasal inoculation with 10^5^ CFU *N*. *lactamica* (wild type strain Y92-1009) at 36+0 to 37+6 weeks gestation (figure 1). Upper respiratory samples and breastmilk will be collected from mother–infant pairs 1 day, 1 week and 1 month post partum, as well as an umbilical cord blood sample at delivery and an infant venous blood sample at 1 month post partum. Adverse events and relevant clinical data (including mode of delivery, infant feeding and use of antimicrobials) will be recorded. Samples will be analysed by microbiological culture, targeted PCR and sequencing to determine *N. lactamica* Y92-1009 presence, colonisation density and longitudinal microevolution, as well as 16S rRNA gene sequencing to characterise microbiome evolution in mother–neonate pairs.

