### Study visits and procedures

#### Screening

Interested individuals will be reviewed by the study doctor at a screening visit (34+0 to 36+6 weeks gestation), to discuss the study timeline and procedures (table 2) and assess eligibility (box 1). Eligible individuals who provide informed consent at screening will be considered enrolled. A detailed medical history will be taken, followed by pharyngeal and saliva sampling to assess for *N. lactamica* carriage; enrolled volunteers who are already naturally colonised with *N. lactamica* will not be inoculated. However, they will be invited to remain in the study as an opportunistic comparison cohort, and will complete all postpartum visits and sampling as for the inoculated mother–neonate pairs (table 2).

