*Neisseria lactamica* nasal inoculation		+ (Unless already colonised)				
Nasopharyngeal swabs (mother)	+	+	+	+	+	+
Oropharyngeal swabs (mother)	+	+	+	+	+	+
Saliva swabs (mother)	+	+	+	+	+	+
Nasopharyngeal swabs (infant)			+	+	+	+
Saliva swabs (infant)			+	+	+	+
Umbilical cord blood			Optional			
Infant venous blood (2 mL)					Optional	Optional
Maternal breast milk			Optional	Optional	Optional	Optional
Maternal venous blood (5 mL)						Optional
Oropharyngeal and saliva swabs (under 5 years)						Optional

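### For inoculated women M counts any N. lactamica strain but N requires Y92-1009, so a mother carrying only a wild strain enters the denominator with no Y92 to transmit

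*Protocol article*

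**What the plan says.** All references are to the Protocol article.

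- **Statistical analysis** gives the primary endpoint as N/M. The denominator is "M=Number of mothers colonised with" *N. lactamica*, with no strain named. A woman counts as colonised on a positive upper respiratory culture at one or more visits, and visits before inoculation are not excluded. N counts neonates up to day 31 who share their own mother's strain. That match is established by Y92-specific "PCR for inoculated volunteers, or whole genome sequencing for volunteers already naturally carrying *N. lactamica* at screening".
- **Screening** (34+0 to 36+6 weeks) takes throat and saliva samples to look for carriage, and withholds inoculation from "enrolled volunteers who are already naturally colonised with" the species. Table 2 repeats the condition as "Unless already colonised", without naming the sample or date that decides it.
- **Study overview** and Table 2 place inoculation at 36+0 to 37+6 weeks. Table 2 also lists maternal swabs at that visit.
- ***N. lactamica* identification** gives the turnaround: "Following 24–48 hours incubation, colonies with typical" morphology go on to identification. A swab taken at the inoculation visit cannot be read before the inoculum is given that day.
- **Study hypothesis, objective and endpoints** and **Sample size** both frame the question as transfer from women colonised by the inoculum. The benchmark is worked out for 18 such women.

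**The concern.** M is defined by species and N, for inoculated pairs, by strain. The two agree only if every *N. lactamica* cultured from an inoculated woman is Y92-1009. Nothing in the plan secures that. An inoculated woman may carry a wild strain that screening missed, that she acquired between screening and inoculation, or that she acquired later. If she never takes Y92, her wild isolate still puts her in M. Her infant can then enter N only by carrying Y92, which she could not have passed on. If the infant shares her wild strain, the pair meets the plain description of N but fails the rule used to confirm it, because the sequencing route is reserved for women already carrying at screening.

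The result is a denominator that includes women outside the target population, and a primary proportion that is too low. The same women would also be read as successful takes of the inoculum, although maternal take is part of the hypothesis and not a listed endpoint. The never-inoculated comparison cohort is not affected.

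**Working it through.** **Inputs from the document:** 20 inoculated; 90% expected take, hence 18 colonised; 2.3% natural infant carriage at 1 month; benchmark 22% (95% CI 2.3% to 41.7%); 10% baseline natural maternal carriage. **Assumptions, not in the document:** culture sensitivity 80–90% at screening; 1–5% acquire a wild strain between screening and inoculation.

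**1. The gap.** Longest: 37+6 minus 34+0 = 265 − 238 = 27 days. Shortest: 0 days, because the two windows overlap.

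**2. The plan's own interval.** p ± 1.96·√[p(1−p)/(n−1)] with p = 0.22 and n = 18: √(0.1716/17) = 0.1005, half-width 0.197, giving 2.3% to 41.7%. This reproduces the stated figure. With divisor n it would be 2.9% to 41.1%.

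**3. Wild carriage at inoculation among screen-negative women.**
- Missed at screening: 0.10×0.10/0.91 = 1.1%, to 0.10×0.20/0.92 = 2.2%.
- Adding 1–5% acquisition gives about 2–7%, or 0.4–1.4 of 20 women.

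**4. Of these, the women who never take Y92.** Only they are wrongly in M.

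| Assumption about take | Affected share | Expected of 20 | Chance of at least one |
|---|---|---|---|
| 90% take, independent of wild carriage | 10% × (2–7%) = 0.2–0.7% | 0.04–0.14 | 1−0.998²⁰ = 4%, to 1−0.993²⁰ = 13% |
| Resident strain always blocks Y92 | 2–7% | 0.4–1.4 | 1−0.98²⁰ = 33%, to 1−0.93²⁰ = 77% |

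Wild strains acquired after inoculation would add to these figures; the document offers nothing from which to size that route.

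**5. What one such woman does to N/M.** Four is the smallest count out of 18 above the 22% benchmark (3/18 = 16.7%).

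| N/M | Estimate | Lower limit, divisor n−1 | Lower limit, divisor n | Exact lower limit |
|---|---|---|---|---|
| 4/18 | 22.2% | 2.5% | 3.0% | 6.4% |
| 4/19 (one wild-only mother added) | 21.1% | 2.2% | 2.7% | 6.1% |
| 4/17 (one of the 18 was wild-only and is removed) | 23.5% | 2.7% | 3.4% | 6.8% |

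By the plan's own formula, 4/18 clears 2.3% and 4/19 does not. By either of the other two intervals, all three results clear it.

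**The case against.** Four points can be made against this.

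- **Size.** A reader might infer that every woman naturally colonised at inoculation is misclassified. The documents do not support that. They expect about 90% take at this dose, and a woman who carries a wild strain and also takes Y92 is properly in M, with her infant properly judged on Y92. The 2–7% figure applies only if a resident strain always blocks Y92, which is stated nowhere. Screening also swabs three maternal sites (nasopharynx, oropharynx, saliva), which makes a missed carrier less likely, and 27 days is the extreme gap. This point stands, and the range in the working reflects it.
- **The benchmark.** A reader might infer that one such woman overturns the result. The crossing at 4/19 is a near miss by one approximate interval (2.2% against 2.3%). The 22% figure was also derived for 18 mothers; the same formula for 19 gives about 21.2%, which 4/19 misses by roughly 0.1 percentage point. This stands too: the crossing illustrates sensitivity at the boundary and no more.
- **The data are already planned.** The PCR includes a locus that recognises non-Y92 strains, paired isolates are to be sequenced if any neonate is colonised, and swabs are taken at the inoculation visit. That is correct, but the endpoint rule uses none of it to decide which inoculated women belong in M. Nor is this detail left to a fuller document: the article states numerator, denominator and strain rule outright, and they do not match.
- **Scoring.** Not counting a shared wild strain as transfer is right when the question is carriage induced by inoculation. Agreed. The fault is that the mother stays in M. The bias is downward, so it cannot create a false claim of transfer.

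**Conclusion.** The mismatch is real and lies in the stated primary-endpoint rule. An inoculated mother who carries only a non-Y92 strain and never takes Y92 is counted in M although she has no Y92 to transmit, so N/M understates transfer from women colonised by the inoculum. The number affected is probably small. On the assumed 2–7% wild carriage at inoculation, the chance of at least one such woman among 20 lies between 4–13% and 33–77%, depending on whether wild carriage leaves Y92 take unchanged or always prevents it. With M near 18, one woman moves the estimate by about one percentage point (22.2% to 21.1%, or 23.5% to 22.2%). That matters only close to the benchmark, and it changes the comparison with 2.3% only under the plan's own interval. It is worth correcting because the rule is wrong as written and the correction costs almost nothing.

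**What to change.** In Statistical analysis, for inoculated volunteers:

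1. Define M as mothers with at least one post-inoculation isolate confirmed as Y92-1009 by the strain-specific PCR.
2. Use the culture from the inoculation visit retrospectively: a non-Y92 isolate there flags natural carriage at inoculation.
3. Report inoculated pairs who share a non-Y92 strain, confirmed by whole genome sequencing, on a separate line, neither as transfer nor as failed transfer.

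The isolates are stored, the PCR exists, the inoculation-visit swab is already taken, and sequencing of paired isolates is already planned if any neonate is colonised. No visit or inoculation rule changes. The cost is a change of wording and PCR on maternal isolates. M may be slightly smaller, and the interval correspondingly wider. The change should be made before infant results are known, so that the denominator is not chosen in their light.

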### Study hypothesis, objective and endpoints

We hypothesise that nasal inoculation of pregnant women with 10^5^ CFU *N*. *lactamica* strain Y92-1009 will result in maternal upper respiratory *N. lactamica* colonisation; and that horizontal transmission of upper respiratory *N. lactamica* will occur from experimentally-colonised women to their infants by 4 weeks post partum.

This study aims to investigate this hypothesis, and to characterise the safety, colonisation kinetics and microbiome impact of nasal *N. lactamica* inoculation in pregnancy on mother–neonate pairs (table 1).

**Table 1 T1:** Primary, secondary and safety study endpoints

Primary endpoint Confirmation of neonatal (0–31 days) *Neisseria lactamica* colonisation by selective culture of nasopharyngeal and saliva samples.	Secondary endpoints Confirmation of neonatal *N. lactamica* Y92-1009 colonisation by strain-specific PCR. *N*. *lactamica* colonisation density in inoculated volunteers compared with their infants across study time points and sample niche. Microbiome composition across study time points and sample niche in inoculated volunteers compared with their infants, and in colonised compared with uncolonised infants. *N*. *lactamica* genome sequence for isolates derived from inoculated volunteers compared with their infants across study time points and sample niche.
		Safety endpoints Percentage of inoculated volunteers with adverse reactions or serious adverse events within the study period. Percentage of neonates with serious adverse events within the study period.

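### As worded, the primary proportion N/M counts naturally colonised, never-inoculated mothers and their infants, although the hypothesis and the 22% criterion concern inoculated mothers only

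*Protocol article*

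**What the plan says.** All references are to the protocol article.

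- **Statistical analysis.** The primary endpoint is one proportion, N/M. The denominator is "M=Number of mothers colonised with *N. lactamica", with no mention of inoculation. The numerator is neonates "colonised with the same strain of *N. lactamica* as their own mother". Colonised means a positive upper respiratory culture on at least one visit. Strain identity is confirmed by Y92-specific PCR "for inoculated volunteers, or whole genome sequencing for volunteers already naturally carrying" the organism at screening. A subgroup analysis is then planned "to compare inoculated mother–infant pairs with naturally colonised mother–infant pairs".
- **Screening.** "enrolled volunteers who are already naturally colonised with *N. lactamica* will not be inoculated"; instead, "they will be invited to remain in the study as an opportunistic comparison cohort", with all postpartum visits and sampling.
- **Study hypothesis, objective and endpoints.** The transmission hypothesis concerns passage of the organism "from experimentally-colonised women to their infants by 4 weeks post partum".
- **Sample size.** The >22% criterion (95% CI 2.3% to 41.7%) rests on observed infant "colonisation for a sample of 18 experimentally-colonised volunteers". Exceeding it is read as showing that inoculation-induced carriage is above the natural infant carriage of 2.3%.

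**The concern.** The primary endpoint and the criterion meant to interpret it describe different groups of women. Screening is itself a study visit with respiratory sampling, so a natural carrier satisfies the definition of colonised, and hence of M, before anyone is inoculated. The same-strain rule then supplies the method by which her infant would be counted in N.

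A pair in which the mother was never inoculated carries no information on transfer induced by inoculation. If such pairs share strains often, they raise the primary proportion; if they do not, they dilute it. Either way the headline figure depends partly on how many natural carriers happen to be screened and stay in the study. The cohort meant as the comparison would also sit inside the figure it is compared with.

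**Working it through.** **1. Reproduce the stated criterion.** A two-sided 95% Wald interval with n-1 in the standard error is p ± 1.96 × √[p(1-p)/(n-1)]. With p = 0.22 and n = 18:

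- √(0.22 × 0.78 / 17) = 0.1005, and 1.96 × 0.1005 = 0.1969
- interval: 2.31% to 41.69%

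This matches the article's 2.3% to 41.7%. Dividing by n = 18 instead gives 2.86% to 41.14%, which does not match. On 18 infants both forms need at least 4/18 = 22.2% for the lower limit to exceed 2.3%.

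**2. Expected number of natural pairs.** The Sample size section gives at least 24 screened and 10% natural carriage. The expectation is 24 × 0.10 = 2.4, and the binomial probability of at least two carriers among 24 is 0.71. I use two pairs. The number is lower if carriers do not take up the invitation to stay.

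**3. Inoculated pairs alone and with two natural pairs added.** The entries are lower 95% limits, to be compared with 2.3%.

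| Result | Proportion | Wald, n-1 | Wald, n | Clopper-Pearson |
|---|---|---|---|---|
| 3/18 inoculated only | 16.7% | -1.05% | -0.55% | 3.58% |
| 3/18 + 2/2 = 5/20 | 25.0% | 5.53% | 6.02% | 8.66% |
| 4/18 inoculated only | 22.2% | 2.46% | 3.02% | 6.41% |
| 4/18 + 0/2 = 4/20 | 20.0% | 2.01% | 2.47% | 5.73% |

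**4. Upward change (fail to pass).** On the interval behind the article's figures, 3/18 fails and 5/20 passes. The other intervals also allow an upward change, though at different counts:

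- Plain Wald: the same step, from 3/18 to 5/20.
- Clopper-Pearson: 2/18 (1.38%, fails) plus 2/2 becomes 4/20 (5.73%, passes).
- Wilson: 1/18 (0.99%, fails) plus 2/2 becomes 3/20 (5.24%, passes).

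**5. Downward change (pass to fail).** 4/18 passes. After dilution to 4/20, the lower limit is 2.01% with n-1 Wald, which fails, and 20% is also below a literal 22% cut-off. With plain Wald it is 2.47% and with Clopper-Pearson 5.73%, so both still pass.

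**6. Sensitivity to the number of natural pairs.** With one pair, 3/18 + 1/1 and 4/18 + 0/1 both give 4/19 = 21.1%. The n-1 Wald lower limit is 0.2105 - 1.96 × √(0.2105 × 0.7895 / 18) = 2.22%, so on this interval there is no upward change, but 4/18 would be pulled below the bar. With no natural pairs in the study, pooling has no effect.

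**The case against.** The strongest reply is that pooling is inferred from terse wording. The article never says the groups are combined. The planned inoculated-versus-natural comparison needs N/M in each group, so a shared definition has to cover both methods of strain confirmation. The hypothesis and the comparison-cohort label both suggest that separate calculation was intended. The inoculated-only proportion can be recovered from the subgroup analysis, no data are lost, and this is a small proof-of-concept study with a pragmatic sample size.

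Much of this is fair as an account of intent, and it limits the damage. It does not remove the defect. The article states one primary proportion, gives its denominator without an inoculation condition, and nowhere says that it is computed by group. Recovering the right figure as a subgroup result leaves the main question answered outside the primary endpoint. Nor is this a detail left to a fuller document: the stated definition conflicts with other sections of the same article.

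Three stronger readings are tempting but not supported:

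- *The conclusion flips in both directions.* The downward change appears only with the n-1 Wald interval, or if the 22% cut-off derived for n = 18 is carried over to a different n.
- *The comparison with natural carriage is circular.* The 22% and 2.3% figures stand only in the Sample size section, for experimentally colonised mothers. The Statistical analysis section states no test of N/M against either, so circularity follows only if that criterion is applied to the pooled proportion.
- *The inoculated-versus-natural comparison can never reach p<0.05 with two natural pairs.* This is not so in general. Fisher's exact test for 2/2 versus 4/18 gives 15/190 = 0.079, but 2/2 versus 2/18 gives 6/190 = 0.032. The article also names no test for this comparison, so there is no ground for asking that one be removed.

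**Conclusion.** The point holds as a mismatch between the stated primary endpoint and the question the study asks. Read as written, N/M includes never-inoculated pairs in numerator and denominator, contrary to the hypothesis, the comparison-cohort role and the basis of the 22% criterion.

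The size is modest in pairs, about two added to 18, but enough to turn a borderline failure into a pass. The illustration rests on two assumptions: that about two natural carriers stay in the study, and that the Sample size criterion is applied to N/M. It also needs an inoculated result just below the bar and, in the example given, same-strain colonisation in both natural infants. The article gives no mother-to-infant transmission rate for natural carriers, so the likelihood of that case cannot be stated. The mismatch in definition depends on none of these assumptions.

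**What to change.** In the Statistical analysis section, define the primary endpoint for inoculated volunteers only:

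- M = inoculated mothers colonised with *N. lactamica* after inoculation.
- N = infants of those mothers, aged 0–31 days, colonised with PCR-confirmed Y92-1009.

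Move the whole genome sequencing rule for natural carriers to the description of the comparison cohort, and report those pairs separately with their own n/m. The planned comparison of the two groups can stay.

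The cost is a change of wording. No visit, sample or assay is added, the planned 18 in the Sample size section is unchanged, and the denominator is smaller than the pooled one by the number of natural pairs, about two.
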